## Abstract

**Background:**

Cardiovascular disease (CVD) is the leading cause of death globally. Community pharmacist intervention studies have demonstrated clinical effectiveness for improving several leading individual CVD risk factors. Primary prevention strategies increasingly emphasise the need for consideration of overall cardiovascular risk and concurrent management of multiple risk factors. It is therefore important to demonstrate the feasibility of multiple risk factor management by community pharmacists to ensure continued currency of their role.

**Methods/Design:**

This study will be a longitudinal pre- and post-test pilot study with a single cohort of up to 100 patients in ten pharmacies. Patients aged 50-74 years with no history of heart disease or diabetes, and taking antihypertensive or lipid-lowering medicines, will be approached for participation. Assessment of cardiovascular risk, medicines use and health behaviours will be undertaken by a research assistant at baseline and following the intervention (6 months). Validated interview scales will be used where available. Baseline data will be used by accredited medicines management pharmacists to generate a report for the treating community pharmacist. This report will highlight individual patients' overall CVD risk and individual risk factors, as well as identifying modifiable health behaviours for risk improvement and suggesting treatment and behavioural goals. The treating community pharmacist will use this information to finalise and implement a treatment plan in conjunction with the patient and their doctor. Community pharmacists will facilitate patient improvements in lifestyle, medicines adherence, and medicines management over the course of five counselling sessions with monthly intervals. The primary outcome will be the change to average overall cardiovascular risk, assessed using the Framingham risk equation.

**Discussion:**

This study will assess the feasibility of implementing holistic primary CVD prevention programs into community pharmacy, one of the most accessible health services in most developed countries.

**Trial registration:**

Australia and New Zealand Clinical Trial Registry Number: ACTRN12609000677202

## Background

Cardiovascular disease (CVD) is the leading cause of death globally, accounting for an estimated 17.1 million deaths per annum - 29% of all deaths [1]. The relative contribution of CVD to the burden of disease remains high in countries with low-, middle-, and high incomes [1]. Despite significant gaps in research, there is sufficient evidence (particularly from developed nations such as the United States and United Kingdom) to suggest that the primary prevention of CVD represents a cost effective approach to reducing this burden [2].

There is a cluster of highly prevalent CVD risk factors in many developing and most developed countries including Australia which can be controlled or avoided: tobacco smoking, hypertension, overweight and obesity, physical inactivity, dyslipidaemia (high cholesterol), poor nutrition and diabetes [1,3]. Significant evidence-treatment gaps remain in the management of each of these, culminating in substantially elevated incidences of CVD in most countries. Community pharmacists are highly accessible health professionals in most communities and have demonstrated an effective role in the management of several of these risk factors [4-7]. Guidelines on primary CVD prevention now highlight the importance of overall CVD risk assessment rather than traditional individual risk factor assessment, resulting in a much greater emphasis on multiple risk factor management [8-13].

The expertise of community pharmacists in medicines management including adherence screening and management, and a growing role in health promotion has resulted in several studies demonstrating effective pharmacist involvement with multiple CVD risk factor management [14-16]. However, we are not aware of any multiple risk factor study specifically examining structured, pharmacist-led disease state management programs for primary CVD prevention in a non-diabetic population. The *Pharmacist Assessment of Adherence, Risk and Treatment in Cardiovascular Disease (PAART CVD) *was developed as a pilot project to address this evidence gap.

This paper describes the research protocol developed for the PAART CVD project, a community-pharmacy based CVD primary prevention pilot project in a non-diabetic, adult population. We also identify the theoretical framework, local issues affecting implementation decisions, and gaps in current knowledge experienced to facilitate future adaptation.

### Goals of research

1. To assess the feasibility of implementing a primary CVD prevention program in a community pharmacy setting

2. To measure changes to cardiovascular health for patients receiving the PAART CVD intervention.

## Methods and Design

### Study design and setting

This is a longitudinal pre- and post-test study to be undertaken with a single cohort of patients. Ten pharmacies from two States (Victoria and Tasmania) will be recruited - five each from rural and metropolitan locations. Each pharmacy will be asked to approach a convenience sample of patients meeting the inclusion criteria, with a goal of recruiting 10 participants per pharmacy. Local general practices and general practice organisations will be informed about the project.

### Outcomes examined

The primary outcome for the intervention will be the average change to estimated 5-year risk of primary onset of CVD between baseline and six months calculated using the New Zealand CVD risk scores [11], a modified version of the Framingham-based risk equation [17]. Secondary health outcomes include change to blood pressure, lipid profile, random blood glucose, waist, body mass index (BMI), and depression score.

### Pharmacist training

Over two consecutive days, pharmacists from recruited pharmacies will attend training focussed on the following key topics:

• health promotion and behavioural change

• overall CVD risk and CVD risk assessment

• medicines adherence

• medicines management for cardiovascular risk factors

• lifestyle modification (diet, physical activity, weight management, alcohol consumption)

• antiplatelet use for primary CVD prevention

• smoking cessation

• managing patients who screen positively for diabetes, alcohol abuse or depression; and

• General Practitioner (GP) and other health professional engagement.

All training, including training materials, will be consistent with relevant national guidelines and will be tailored to suit a generalist community pharmacist audience. Emphasis will be placed on the need for pharmacists to act within their professional competencies and take appropriate action if situations arise outside their competencies (e.g. patient screens positive for depression). Written guidelines will be provided to identify patients with complex or urgent clinical needs that warrant referral to a GP or another health professional (e.g. dietitian). Pharmacists will also be advised on options for referral (e.g. how to access specialist dietary or smoking cessation advice) when they might deem it appropriate.

### Subject eligibility criteria

Inclusion criteria

To be eligible for participation in the study, patients need to be

• aged 50-74 years

• currently taking one or more medicines for cholesterol and/or hypertension, and

• free from established cardiovascular disease, diabetes or a cardiovascular event.

Individuals will be excluded from the study in the following instances:

• patients with a complex debilitating coexisting medical condition

• target organ damage

• any cognitive impairment

• reliance on a carer or living in a residential aged care facility

• recent hospital inpatients who were medical admissions and discharged less than four weeks prior to recruitment

• non-English speaking

• living more than 40 km from a participating pharmacy

• patients who have received a Home Medicines Review (HMR) in the past 12 months

• deemed inappropriate for the intervention by the patient's GP; or

• patients of GPs who express a desire not to have any involvement with this project.

### Patient recruitment

Pharmacists will initially be asked to conduct a simple pre-screening of potential participants based on the inclusion criteria outlined above. The information required (CVD history, use of CVD medicines, and age) is quick and easy to obtain from dispensing records and patient interview. Potential participants expressing interest will be provided with written patient information and an Expression Of Interest (EOI) form to be completed and returned to researchers.

Upon receipt of EOIs or direct patient-initiated contact via a free telephone number, a formal assessment of all eligibility requirements will be undertaken by researchers and a provisional baseline assessment date agreed. If eligible, consent must be obtained to contact their GP in writing and to provide the GP with an opportunity to comment on the appropriateness of participation. Written consent for participation and sharing of health information with relevant health professionals is to be provided by patients prior to baseline assessment.

### Patient data collection

Baseline and final (6 month) patient information will be collected by trained research assistants (RAs). This process will take 60-90 minutes on both occasions and can take place in the patient's home (preferred), or in a private area at the pharmacy or their workplace. Assessment involves anthropometric and Point Of Care (POC) biomedical testing, and an administered questionnaire using validated scales where possible. Lipid profiles and fasting blood glucose levels will be obtained using Cholestech LDX^® ^Analyzers [18,19], in accordance with instructions provided by the manufacturer. This device uses finger-prick testing and provides results within 10 minutes. Quality control samples will be used to validate the machine prior to measurements. Patients will be advised that the most accurate results for cholesterol and blood glucose levels would be obtained by fasting 12-16 hours prior to the initial assessment interview and testing, and to take their medications as normal on the day of clinical assessment. Fasting time will be recorded to aid clinical interpretation.

When the patient is rested, blood pressure (BP) will be measured using an Omron 1A1B^® ^automated BP monitor in accordance with WHO MONICA Monitoring of Trends and Determinants of Cardiovascular Diseases and the European Health Risk Monitoring protocols [20,21] amended for use with an automated monitor. The average of two measurements taken 2-3 minutes apart will be used, but if systolic BP measurements differ by 10 mmHg or greater, or diastolic BP differ by 6 mmHg or greater, a third reading will be taken. In this instance the average of the two closest systolic and two closest diastolic BP measurements will be used to define the BP. The RA will advise patients to seek immediate medical attention if systolic BP is 180 mmHg or greater, or if diastolic BP is 110 mmHg or greater. Weight, height, and waist and hip circumferences will be measured in accordance with the EHRM protocol [21].

The remainder of the assessment will consist of a researcher-administered questionnaire (all interviewing researchers have pharmacy qualifications). This questionnaire, which includes several validated survey instruments, covers a range of health indicators:

• demographic and social information, including some questions based on the WHO MONICA (MONItoring of CArdiovascular events) protocol [21], as adapted for the Greater Green Triangle Chronic Disease Risk Factor Studies [22]

• brief patient medical history and family history of CVD events

• details of current medicines

• details of recent testing for CVD risk factors prior to baseline

• adherence to current medications advice using the Tool for Adherence Behaviour Screening (TABS) [23] and the Morisky scale [24]

• smoking, physical activity and weight management status - including some screening questions from the 'Lifescripts' program [25] and questions from surveys used by the Greater Green Triangle Chronic Disease Risk Factor Studies [22]

• nutrition and adherence to national dietary guidelines, based on Dietary Guidelines for Australian Adults (2003) [26] and using a number of questions from the National Nutrition Survey 1995 [27], and the Cancer Council of Victoria Food Frequency Questionnaire [28]

• screening for excess alcohol consumption using the AUDIT C tool [29]

• screening for depression using the Center for Epidemiological Study of Depression Scale (CES-D) [30]

• quality of life measure using the SF-12v2 Health Survey™ (Ware et al, 2007) [31].

Pharmacists will be asked to supply medicines dispensing data for the six months' period prior to baseline data collection and the six months prior to follow up data collection. To account for medicines collected elsewhere, patients will be asked during their interviews to recall any quantities of medicines obtained elsewhere for the specified period.

### Intervention part one: accredited pharmacist review

Using relevant national clinical guidelines as the benchmark for management, pharmacists accredited to undertake collaborative, structured medicines management reviews in community settings (known as 'Home Medicines Reviews') will produce a written report for each patient highlighting the estimated 5-year CVD risk, suboptimal CVD risk factors, and medication adherence and other medicines use issues (see additional file 1 for template). The report will also suggest patient treatment goals and opportunities for beneficial lifestyle changes and improved medicines management to achieve goals. This report will be provided to the patient's community pharmacist with summaries for the patient and their general practitioner.

### Intervention part two: community pharmacist facilitating patient change

Community pharmacists will be trained to deliver their interventions in accordance with the Health Action Process Approach (HAPA) [32] to behaviour change over five counselling sessions conducted at monthly intervals. The emphasis in counselling progresses from change motivation initially (via improved self-efficacy, belief in the need for change and belief that change will generate positive outcomes), through to change maintenance and relapse prevention strategies. Written, achievable goals will be encouraged.

The first session with the patient will prioritise basic health education regarding individual CVD risk and the benefits of potential treatments. It also establishes acceptable goals for the treatment process through patient consultation, and how these might be achieved. Finally, the pharmacist will discuss with the patient any specific medication changes identified in the baseline report that are recommended to improve adherence to CVD guidelines. Community pharmacists will not be trained or asked to make interventions related specifically to diabetes or mental health issues, but will be alerted to any suboptimal assessment results in these areas and asked to discuss with the patient the potential need for GP input. Such issues will also be identified in the baseline assessment summary provided to the GP.

If a patient's overall 5-year CVD risk score is 5% or less (considered very low risk) they will be advised to discuss with their pharmacist whether they are likely to benefit from continuing with the intervention. The decision to continue will be left to the pharmacist and the patient. Pharmacists will be expected to assess and document patient motivation to undertake various medication and lifestyle changes. Following discussion with each patient, the pharmacist will then forward the clinical summary to the patient's GP with any additional comments considered relevant.

Subsequent sessions will involve: ensuring necessary changes to medicines have been made; monitoring of medicines adherence especially for new medicines; linking patients with local health and other services that provide relevant patient support; initiating lifestyle change and supporting maintenance and relapse prevention. Throughout these sessions, patient progress towards goals will be continually reassessed, as will be the goals themselves. GP input to patient treatment plans will also be invited.

### Primary outcomes

The primary outcome for the PAART CVD intervention is the average change to overall estimated 5-year risk of CVD onset, calculated using the New Zealand adaptation of the Framingham-based CVD risk score [11,17].

### Secondary outcomes

Other outcomes examined include:

• Changes to individual modifiable CVD risk factors (blood pressure, lipid profile, Body Mass Index, waist circumference, smoking status, depression)

• changes in medicines adherence assessed using Morisky [24] and TABS scales [23]; and

• changes in key health behaviours (physical activity, diet, alcohol intake, weight management).

Additional outcomes to be assessed include stakeholder satisfaction (GP, pharmacist, patient) and process audit based on community pharmacist documentation of counselling sessions.

### Sample size

With 80 subjects this study would have a 90% power to show an absolute reduction in risk of 1% based on a standard deviation in the change of risk of 2.7% with a two sided p-value of 0.05. To account for potential subject drop out and loss to follow-up of 20% we will aim to recruit 100 subjects.

### Statistical analysis

Univariate comparisons between groups will be conducted using chi-square test for equal proportion (or Fisher's exact tests where numbers are small) and reported as numbers and percentages. Continuous normally distributed variables will be compared using Student's t-tests and reported as means (standard error) whilst non-parametric data will be compared using Wilcoxon rank-sum tests and reported as medians (interquartile range). Pairwise differences between pre and post values will be calculated using paired t-tests for normally distributed data and Wilcoxon sign rank tests for non-normally distributed data. To account for the large number of comparisons being made, we will employ a reduced 2-sided p-value of 0.01 to indicate clear statistical significance.

If any parameter from POC finger prick testing is found to be outside the measurable range for the machine, the value of the closest measurable limit will be given to that patient.

Health behaviours will largely be measured using existing scales associated with the survey instruments incorporated into baseline and follow-up assessment. For the dietary assessment, no validated tools are available for use in an Australian population so a study-specific tool has been devised. This tool is a 13-item questionnaire addressing dietary quality in this study population and using previously validated questions from the National Nutrition Survey and Cancer Council of Victoria Food Frequency Questionnaire relating to the nutrients of concern for primary prevention of CVD [27,28]. Responses for each item will be scored between zero (least healthy response option) and 10 (healthiest option) - consistent with the developing literature in this area of nutrition research [33]. This scoring allows for an overall diet score to be generated ranging from 0 to 130.

The general quality of dietary intake will be interpreted using the guidance provided in table 1.

**Table 1 T1:** Scoring mechanism used to assess overall quality of dietary intake

Diet score using nutrition tool	Interpretation
104-130	High level of compliance with CVD dietary guidelines (80% or more)

78-103	Medium level of compliance with CVD dietary guidelines (60-79%)

77 or less	Low level of compliance with CVD dietary guidelines (59% or less)

This score allows a good estimate of the level of adherence to key diet-related behaviours. Constituent elements of the 13-item questionnaire also allowed development of sub-scales for these areas of significant influence on cardiovascular health:

• fruit and vegetable intake (soluble fibre and antioxidants)

• saturated fat and total fat intake

• omega-3 fatty acid intake

• fibre intake (insoluble fibre); and

• salt intake.

The sub-scales enable community pharmacists to deliver more tailored dietary advice to participants.

The study protocol was approved by Monash University Human Research Ethics Committee (HREC), University of Tasmania HREC, Flinders University Social and Behavioural Research Ethics Committee and the Australia and New Zealand Clinical Trials Registry (Trial Number ACTRN12609000677202).

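### Patients are recruited and counselled within ten pharmacies, but the power and the paired tests treat all 80 as independent; if changes correlate within pharmacy, the standard error is too small and the power too high

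*Protocol article*

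**What the plan says.** **Structure.** Under Study design and setting, "Ten pharmacies from two States (Victoria and Tasmania) will be recruited - five each from rural and metropolitan locations", and each approaches its own convenience sample "with a goal of recruiting 10 participants per pharmacy". The abstract says: "Community pharmacists will facilitate patient improvements in lifestyle, medicines adherence, and medicines management over the course of five counselling sessions with monthly intervals". The section on the second part of the intervention confirms that the patient's community pharmacist runs these sessions.

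**Sample size.** "With 80 subjects this study would have a 90% power to show an absolute reduction in risk of 1" per cent, "based on a standard deviation in the change of risk of 2.7% with a two sided p-value of 0.05". The recruitment target follows: "To account for potential subject drop out and loss to follow-up of 20% we will aim to recruit 100 subjects". No ICC or design effect appears.

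**Analysis.** "Pairwise differences between pre and post values will be calculated using paired t-tests for normally distributed data"; the Wilcoxon signed-rank test is named for non-normal data. There is no pharmacy term, mixed model, generalised estimating equation or cluster-robust variance. The limitations section does not mention clustering.

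**The concern.** Patients in one pharmacy share the staff who counsel them, and each pharmacy approaches its own patients. Half the sites are rural and half metropolitan. The article expects delivery to vary: its Discussion says process audit data are collected to see how well pharmacists keep to the behavioural approach. It is therefore plausible that some pharmacies achieve larger changes than others.

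Pairing does not deal with this. It removes stable differences in level between patients and between pharmacies. It leaves between-pharmacy variation in the change, which is the quantity tested. With a positive ICC of the change score, and inference meant to reach beyond these ten pharmacies, the plain paired tests give an interval that is too narrow and a type I error above nominal. The 90% power is then optimistic too.

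An article may leave detail to an analysis plan that is not shown. Here, however, the article itself fixes both the test and the basis of the sample size.

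**Working it through.** **Inputs from the article:** 80 evaluable patients; difference 1 percentage point; SD of change 2.7 points; two-sided 0.05; 10 pharmacies; 10 recruited per pharmacy; 20% loss.

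**Derived:** 10 × (1 − 0.20) = 8 evaluable per pharmacy.

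**Assumed:** ICC of the change score from 0.01 to 0.10, because the article gives none; equal cluster sizes; 2.7 as the total SD of change.

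**1. The plan's own figure.**
- Normal approximation: n = [2.7 × (1.960 + 1.282) / 1]² = 76.6, so 77. The t-based version needs 79.
- At n = 80 the standard error is 2.7/√80 = 0.302. Power is 91.2% (normal) or 90.5% (noncentral t, 79 df).
- Recruitment: 80/(1 − 0.20) = 100.

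The arithmetic is correct, and independence uses up essentially all of it. Nothing is left over for clustering.

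**2. Design effect.** DE = 1 + (8 − 1) × ICC. Effective n = 80/DE. The standard error is multiplied by √DE.

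**3. Power for a 1-point change at two-sided 0.05.** Noncentrality is 1/(2.7 × √(DE/80)). It is evaluated once with 79 df, which isolates the design effect, and once with 10 − 1 = 9 df, which is the t-test on ten pharmacy means.

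**4. True type I error of the plain paired t-test.** The approximation is 2 × [1 − Φ(z/√DE)], with z = 1.960 (nominal 5%) or 2.576 (nominal 1%). The table gives results from 400,000 simulated trials of 10 × 8 patients, which agree with the formula to within about 0.1 point.

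| ICC (assumed) | DE | Effective n | SE factor | Power, 79 df | Power, 9 df | Type I error, nominal 5% | Type I error, nominal 1% |
|---|---|---|---|---|---|---|---|
| 0 | 1.00 | 80.0 | 1.00 | 90.5% | 83.8% | 5% | 1% |
| 0.01 | 1.07 | 74.8 | 1.03 | 88.6% | 81.3% | 5.8% | 1.3% |
| 0.02 | 1.14 | 70.2 | 1.07 | 86.5% | 78.8% | 6.6% | 1.6% |
| 0.05 | 1.35 | 59.3 | 1.16 | 80.4% | 71.9% | 9.1% | 2.6% |
| 0.10 | 1.70 | 47.1 | 1.30 | 70.9% | 62.0% | 13.2% | 4.7% |

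The ICC 0 row shows the nominal type I error. In the same simulations the t-test on pharmacy means held its nominal 5% at every ICC.

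**5. Separating the two sources of loss.** At ICC 0 the 9-df test already falls from 90.5% to 83.8%, about 7 points. That is the price of having only ten clusters. At ICC 0.02 the total loss is 90.5 − 78.8 = 11.7 points, of which 6.7 come from degrees of freedom and 83.8 − 78.8 = 5.0 from correlation.

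**6. Interval width.** The 95% half-width as planned is 1.990 × 0.302 = 0.60 points. With the pharmacy-level test it is 2.262 × 0.302 × 1.034 = 0.71 at ICC 0.01, and 2.262 × 0.302 × 1.304 = 0.89 at ICC 0.10.

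**The case against.** **The size rests on an assumed ICC.** This stands. The relevant ICC is that of a within-patient change, which may be small, and at 0.01 the plain test errs 5.8% of the time instead of 5%. Delivery is also not wholly a pharmacy matter: accredited pharmacists write the reports, research assistants measure the outcomes, GPs are invited to contribute, and patients may contact the researchers directly. A reader might infer that changes within a pharmacy are certain to be correlated. The article makes that plausible but does not establish it.

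**Setting 62% to 79% against the stated 90% exaggerates the effect of clustering.** This stands too. A reader might attribute the whole gap to correlation, but about 7 points are the cost of 9 df and would be lost at ICC 0.

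**The plan's threshold for clear significance is 0.01.** Across the assumed range the true error at that threshold stays below 5%, so a result that meets it is not easily explained away by clustering. This lowers the stakes. It does not make the standard error or interval right, and at ICC 0.10 most of the protection sought from the stricter threshold is gone.

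**This is a pilot whose first goal is feasibility.** That bears on severity. It does not remove the point, because the article declares a risk-change primary outcome, a 90% power claim and significance levels.

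**A later trial.** A reader might take the article to announce a controlled trial that will use these results. The limitations section says only that validation with larger numbers and a control group would be important if feasibility is shown.

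**Conclusion.** The point holds in direction and is moderate in size. For any positive ICC of the change score, and inference beyond these ten pharmacies, the planned tests understate the standard error and the stated 90% power is too high. Over an assumed ICC of 0.01 to 0.10 the understatement is a factor of 1.03 to 1.30. The signed-rank test rests on the same independence assumption, although the figures above were computed for the t-test only.

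It should be fixed, but it is not critical. A reader might conclude that the estimated change in risk is itself wrong. It is not: clustering leaves the mean change unbiased and affects only its stated precision. The study is an uncontrolled pilot that leaves effectiveness to a larger controlled study. The type I and power figures depend on the assumed ICC, on eight evaluable patients in every pharmacy and on the stated SD. They are a range, not an estimate.

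**What to change.** - **Analysis.** Test the primary change with a linear mixed model that has a random intercept for pharmacy and small-sample degrees of freedom (Kenward-Roger or Satterthwaite), or with a one-sample t-test on the ten pharmacy mean changes. State which before the data are analysed. Treat the continuous secondary changes the same way.
- **Power.** Keep 80 evaluable and 100 recruited, and restate the power over an ICC range, showing the design effect and the 9-df cost separately as in the table.
- **Reporting.** Report the observed ICC of the change in risk for use in any later controlled study, noting that ten clusters estimate it imprecisely.

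**Cost.** Wording only, as patients are already recruited by pharmacy; no extra patients, visits or data. The price is a wider interval (half-width about 0.71 to 0.89 points instead of 0.60 with the pharmacy-level test) and a stated power below 90%. Holding 90% would be a different choice: scaling 80 by the design effect gives about 86 to 136 evaluable patients for ICC 0.01 to 0.10 (107 to 170 recruited), before any allowance for 9 df, and more if they all came from the same ten pharmacies. That is not needed for a pilot.

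### The primary outcome and sample size are on the mean change in 5-year risk, but the only pre-post rule lets the data replace the test of the mean with a signed-rank test

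*Protocol article*

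**What the plan says.** The Primary outcomes section of the protocol article gives the primary outcome as "the average change to overall estimated 5-year risk of CVD onset". The Outcomes examined section adds the timing: "average change to estimated 5-year risk of primary onset of CVD between baseline and six months". Both describe a mean of within-patient changes, which fits the design, a "longitudinal pre- and post-test study to be undertaken with a single cohort of patients".

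The Sample size section works on the same scale. It states "With 80 subjects this study would have a 90% power" for a 1% absolute reduction, "based on a standard deviation in the change of risk of 2.7" percentage points, at a two-sided 0.05.

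The Statistical analysis section has one sentence on within-patient comparisons, which prescribes "paired t-tests for normally distributed data and Wilcoxon sign rank tests for non-normally distributed data". It applies to every pre-post comparison. No other section names a test for the primary outcome or excludes it from this rule.

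**The concern.** The outcome definition and the power calculation commit the study to a mean. The analysis rule commits it to a mean only if the observed data pass as normal. Otherwise the primary test becomes the signed-rank test, whose null hypothesis is that the changes are symmetric about zero. That agrees with a zero mean only when the changes are symmetric.

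Changes in a predicted risk could well be skewed to the left. The section on the community pharmacist intervention expects some participants with a 5-year risk of 5% or less. Their risk has little room to fall, while higher-risk patients can fall further. This is an inference; the documents give no distribution for the change.

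At stake are a p-value that may not belong to the mean reported beside it, and a stated 90% power that holds for one branch of the rule only.

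**Working it through.** **Inputs from the Sample size section:** n = 80 evaluable, mean change 1 point, SD of change 2.7 points, two-sided 0.05, dropout 20%.

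**Step 1: reproduce the stated figure.** For a paired test of the mean:

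- Standardised effect: 1 × √80 / 2.7 = 3.313.
- Normal approximation: Φ(3.313 − 1.960) = Φ(1.353) = 91.2%.
- Noncentral t, 79 df: 90.5%.
- n for 90% power: [(1.960 + 1.282) × 2.7 / 1]² = 76.6, so 77; with the t distribution, 79.
- Recruitment: 80 / (1 − 0.20) = 100.

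The plan's figures reproduce, as a calculation for a test of the mean.

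**Step 2: what the signed-rank test targets under skew.** It responds to the median of pairwise averages of the changes. Take a left-skewed exponential shape (skewness −2) with SD 2.7 and true mean zero. The median of the sum of two unit exponentials is 1.678, so this centre lies at 2.7 × (1 − 1.678/2) = +0.43. The ordinary median is 2.7 × (1 − 0.693) = +0.83. The mean is zero, but the signed-rank target is not.

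**Step 3: simulate the rule.** 10,000 trials per row, n = 80, SD 2.7. Two inputs are assumptions because the documents do not give them: the trigger (Shapiro-Wilk on the differences at 0.05) and the shape of the changes. All figures are at a two-sided 0.05.

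| Shape of changes | Switch to signed-rank | Rejection at mean 0: paired t | Rejection at mean 0: rule | Power at mean −1: paired t | Power at mean −1: rule |
|---|---|---|---|---|---|
| Normal | 5% | 5.5% | 5.5% | 90% | 90% |
| Symmetric, heavy tails (t, 5 df) | 49% | 5.1% | 5.0% | 90% | 94% |
| Gamma, skewness −0.5 | 33% | 5.3% | 6.6% | 92% | 88% |
| Gamma, skewness −1 | 90% | 5.0% | 11% | 93% | 77% |
| Lognormal, skewness −1.75 | 99% | 5.8% | 21% | 95% | 73% |
| Gamma, skewness −2 | 100% | 5.8% | 31% | 96% | 60% |

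Repeat runs moved these by about one percentage point (for example 32% for 31%, 87% for 88%, 97% for 96%). At the 0.01 threshold that the Statistical analysis section sets for clear significance, power under the rule for the three gamma shapes is 70%, 53% and 34%, against 77%, 79% and 82% for the paired t-test.

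With 80 pairs the paired t-test stays near its nominal level over this range. The loss comes from the switch.

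**The case against.** The strongest reply is about scope. The sentence is a general rule for about a dozen outcomes, many of them ordinal or bounded scales for which a signed-rank option is ordinary. A reader could take the average-change definition and the mean-based sample size to imply a t-test for the primary outcome, with details left to an analysis plan. That stands in part: the missing normality criterion is such a detail, and this point does not rest on it. The rule itself, however, is stated, and it reaches the primary outcome. An analysis plan that followed it would inherit the mismatch.

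The second reply is about shape, and it stands. The documents do not say that the changes are skewed. Under symmetric heavy tails the switch holds its level and is more powerful than the t-test (94% against 90% in the table).

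Three stronger readings are tempting, and none is supported:

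- *An ineffective programme would be declared effective in up to 31% of trials.* No. If pre and post values are exchangeable, the differences are symmetric and the signed-rank test is valid. The high rates need most patients to worsen slightly while a minority improve enough to cancel this. For a gamma shape with skewness about −1.4, about 59% worsen. The excess rejections then point almost entirely towards increased risk.
- *The test could point the opposite way from the planned benefit.* Not at the planned effect. With mean −1 and skewness −2, the median is 0.83 − 1 = −0.17 and the signed-rank centre is 0.43 − 1 = −0.57, both still reductions.
- *Fixing the t-test costs no power whatever the shape.* No, as the heavy-tailed row shows.

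**Conclusion.** The point holds as a mismatch between a mean-based primary outcome and sample size and a stated rule that can test something else. Under left skewness of −0.5 to −2, the rule rejects a true zero mean change in about 7% to 31% of trials, against 5-6% for the paired t-test. Its power for the planned 1-point reduction is about 88% to 60%, against 92-96%. These sizes depend on the assumed shapes and the assumed Shapiro-Wilk trigger. With near-normal changes the effect is negligible, and with symmetric heavy tails the rule does slightly better than the t-test.

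The main practical harm is lost power and a p-value that does not match the reported mean. The change should be made, but the matter is moderate. This is a single-arm pilot with feasibility as its first goal, and its limitations section already calls for a larger controlled study to determine effectiveness.

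**What to change.** Add a sentence to the Statistical analysis section: the primary outcome is analysed as the mean change in 5-year risk with its 95% confidence interval and a paired t-test, whatever a normality check shows. Give the signed-rank test and a bootstrap interval for the mean as sensitivity analyses. Limit the existing switch rule to the secondary outcomes.

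The wording change is small and needs no extra data. The stated 90% power, the 80 evaluable and the 100 recruited are unchanged, because they were calculated for this test. The cost is a few points of power relative to the signed-rank test if the changes turn out symmetric with heavy tails.
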